#### Psychometric questionnaires

Questionnaires will be used to rate the pain severity and to evaluate psychosocial constructs. The questionnaires set include painDETECT,^22^ Pain Catastrophizing Scale,^23^ CAP-Knee questionnaire,^24^ Beck Depression Inventory,^25^ Measure of Intermittent and Constant Osteoarthritis Pain questionnaire,^26^ EuroQol 5 Dimension 5 Level (EQ-5DL) questionnaire,^27^ Oxford Knee Score,^28^ Pittsburgh Sleep Quality Index,^29^ Fatigue Severity Scale^30^ and the State-Trait Anxiety Inventory.^31^

At the end of the research visit, the participant will also be asked to fill in a custom-made questionnaire with open-ended questions intended to further investigate aspects of study feasibility and acceptability of the research methods.

#### 6MWT pre and post injection of bupivacaine/placebo

The self-paced 6MWT is aimed to be the functional outcome measure as it can assess the submaximal level of functional capacity. Participants will be requested to undertake a paced walk and are also allowed to stop and rest during performing the test. Participants will be asked to rate the level of knee pain ‘pain this instant’ before and immediately after the test finishes using the 0–100 VAS. The walking course of the 6MWT will be 30 m in length with a mark every 3 m.

#### Quantitative sensory testing

QST is a psychophysical technique evaluating sensory response to standardised mechanical or thermal stimuli. The study will use static pain parameters; pressure pain detection threshold (PPT), and dynamic parameters; temporal summation of pain (TSP) and conditioned pain modulation (CPM). Several lines of evidence suggest that QST can be used to phenotype OA pain based on mechanisms. Enrolled patients will undergo the following QST measures: PPT, TSP and CPM, which will be performed according to a standardised methodology^32–34^ (online supplemental file D).

10.1136/bmjopen-2023-072138.supp4Supplementary data

#### Intra-articular knee joint injection with bupivacaine/placebo

Bupivacaine or sodium chloride 0.9% will be administered via the intra-articular route by a member of the research team (a qualified medic) with appropriate competence in intra-articular injection and the recognition and management of the potential adverse effects. The injection will be carried out under aseptic conditions.

For intra-articular injection, the injected volume of either bupivacaine 0.25% (5 mL) or sodium chloride 0.9% (5 mL) will be the same for each participant. Bupivacaine was selected for the intra-articular injection to achieve analgesia because this was shown in previous studies to significantly reduce knee pain in participants with knee OA 1 hour after injection.^12 13^

#### MRI of the knee before the injection

The participants will also undergo a short structural MRI of the knee at 3 T in order to define synovitis, bone marrow lesions and other structural pathologies in the knee joint. MRI of the knee will be evaluated using the validated semiquantitative MRI Osteoarthritis Knee Score (MOAKS).^35^

#### Brain imaging

The participants will undergo a multimodal MRI scan of the brain at 3 T before and after the intra-articular injection. This study will use the functional MRI (fMRI) protocol from studies in pain imaging that can characterise spontaneous chronic pain.^36–38^

### Outcomes

#### Primary outcome measures

The change in pain score using a 100 mm VAS during the 6MWT from baseline to 1 hour after intra-articular injection with bupivacaine or placebo.The change in pain score using the VAS at rest from baseline to 1 hour after intra-articular injection with bupivacaine or placebo.

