### Experimental procedures

The study involves a single visit in which data will be collected. As per the study protocol (V.1.6, 26 January 2023), the interventions will include an assessment to check patients’ suitability to undergo intervention with a local anaesthetic (bupivacaine) or placebo (sodium chloride 0.9%) intra-articular knee injection. During the visit, all participants will be invited to undertake the following assessments: (1) complete health questionnaires; (2) undergo QST; (3) MRI scan of the knee and brain; (4) perform a 6MWT; and (5) participants will then receive an intra-articular injection of bupivacaine or placebo into the index knee. Assessments will be repeated post intra-articular injection apart from the MRI scan of the knee.

Online supplemental file C contains a detailed description of the study intervention, written in accordance with the Template for Intervention Description and Replication (TIDieR) checklist and guide.^20^

10.1136/bmjopen-2023-072138.supp3Supplementary data

The timings of the postinjection assessments were chosen based on the impact of the timing of bupivacaine administration on its analgesic effects. As the time to peak concentration is 43.4±23.1 min based on previous research using bupivacaine for peripheral analgesia,^21^ there will be a 20 min interval post injection to ensure sufficient time to demonstrate the full effect of local anaesthesia and for the postprocedural care. The postinjection procedures will then be completed between 20 and 60 min post injection.

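### Both primary pain changes are defined at 1 hour, yet the visit schedule lets the readings fall anywhere from 20 to 60 min, and the reason given for starting at 20 min is not supported by the time-to-peak figure cited for it.

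*Protocol article*

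**What the plan says.** Under Primary outcome measures, the article lists two changes in VAS pain, each with the same time point:

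- walking pain: "The change in pain score using a 100 mm VAS during the 6MWT from baseline to 1 hour after intra-articular injection with bupivacaine or placebo"
- resting pain: "The change in pain score using the VAS at rest from baseline to 1 hour after intra-articular injection with bupivacaine or placebo"

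The section on the 6-minute walk test has participants rate their pain "before and immediately after the test finishes using the 0–100 VAS".

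Under Experimental procedures, the article gives a window instead of a time point: "The postinjection procedures will then be completed between 20 and 60 min post injection". Everything except the knee MRI is repeated in it: "Assessments will be repeated post intra-articular injection apart from the MRI scan of the knee". The reasoning for the window starts from a pharmacokinetic figure, "As the time to peak concentration is 43.4±23.1 min based on previous research using bupivacaine for peripheral analgesia", and concludes that "there will be a 20 min interval post injection to ensure sufficient time to demonstrate the full effect of local anaesthesia". Postprocedural care is given as a second reason for the interval.

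The section on the injection justifies the choice of drug by its effect at 1 hour, as it was "shown in previous studies to significantly reduce knee pain in participants with knee OA 1 hour after injection". The Evidence gap section cites the same 1-hour evidence.

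**The concern.** The endpoint definition names a single time, and the schedule names a 40-minute range that ends at that time. Nothing in the visible text says where in the range the two primary readings belong, in what order the tests are done, or how far from 1 hour a reading may be and still count. Two participants could follow the schedule correctly and have their primary pain scores taken at quite different times after injection.

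This matters because of what the study is for. Its primary objectives include collecting data for the main trial's sample size and testing when outcomes should be measured. The Statistical methods section also correlates pain change with sensory-testing and brain-imaging measures, and classes participants as responders if VAS falls by 17 mm or more after injection, with no time attached. If readings are taken at varying times after injection, the drug effect may differ between readings. That can inflate the SD, blur the between-group estimate and move participants across the 17 mm cut-off.

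The second problem is the rationale. The article uses a time-to-peak figure to argue that 20 min is long enough, and the figure points the other way.

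**Working it through.** No sample-size or power figure in the article depends on this point. The target of 50 (25 per group) rests on cited guidance for feasibility studies, so there is no calculation of the plan's own to reproduce. The check has two parts.

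**1. Endpoint time against window**

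Inputs: endpoint at 60 min (Primary outcome measures); window 20 to 60 min (Experimental procedures); walk of 6 min with VAS before and immediately after (6-minute walk section).

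- Length of window: 60 − 20 = 40 min.
- Earliest permitted rest reading: 20 min, which is 60 − 20 = 40 min before the endpoint time.
- Earliest permitted post-walk reading: 20 + 6 = 26 min, which is 60 − 26 = 34 min before it.
- Latest start for a walk that ends inside the window: 60 − 6 = 54 min. If the rest score is the one taken before that walk, it falls at or before about 54 min.

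The definition and the schedule can therefore be met together if the walk is last. The rest score would then be a few minutes short of 60 min. They can also diverge by more than half an hour without any departure from the schedule.

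**2. The 20 min start against the cited time to peak**

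Inputs: mean 43.4 min and ± 23.1 min (Experimental procedures). The article does not define ±; it is taken here as an SD.

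- 20 / 43.4 = 0.46, so 20 min is 46% of the mean, or 43.4 − 20 = 23.4 min before it.
- 43.4 − 23.1 = 20.3 min, so the window opens about one SD below the mean. Mean plus one SD is 43.4 + 23.1 = 66.5 min.

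Share of participants who have reached peak concentration by time t:

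- Normal: Φ((t − 43.4)/23.1). At 20 min, Φ(−1.01) = 0.156. At 60 min, Φ(0.72) = 0.764.
- Log-normal with the same mean and SD: σ² = ln(1 + (23.1/43.4)²) = 0.249 and μ = ln(43.4) − σ²/2 = 3.646. At 20 min, Φ((ln 20 − 3.646)/0.499) = 0.097. At 60 min, 0.815.

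| Distribution | Peaked by 20 min | Peaked by 60 min | Peak inside 20–60 min |
|---|---|---|---|
| Normal | 15.6% | 76.4% | 60.8% |
| Normal truncated at zero (mean and SD before truncation) | 12.9% | 75.6% | 62.7% |
| Gamma | 13.5% | 79.3% | 65.8% |
| Log-normal | 9.7% | 81.5% | 71.9% |

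Across these shapes, about 10% to 16% have peaked when assessments may begin, and about 84% to 90% have not. By 60 min about 76% to 82% have. If ± were not an SD these shares would change, but 20 min would still be less than half the cited mean.

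**The case against.** The strongest reply has four parts.

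- **Not a contradiction.** One hour is the last point of the window, and a walk scheduled last satisfies both statements. This stands. A reader might infer that the two timings cannot both be met; the documents do not show that.
- **Unseen detail.** The trial-flow figure, the supplementary files and the full protocol are not shown and may give a test order and tolerances, which an article commonly leaves out. This stands as a caution, and missing detail alone would be no finding. But the article does state a window and an endpoint time, and as stated they coincide only at one edge. Nor would a test order repair the rationale for 20 min.
- **Concentration is not analgesia.** The cited figure is time to peak concentration, postprocedural care is a second reason for the wait, and a window of 20 to 60 min can be read as bracketing the mean of 43.4 min. All of this stands. It rules out saying by how much an early reading would understate the effect, or that it would. It does not rescue the claim, since the article itself offers this figure as the reason and postprocedural care says nothing about full effect.
- **Timing is already under study.** Outcome timing is a declared feasibility objective, no hypothesis test is planned, and both arms share one blinded schedule, so no bias between arms is identified. This lowers the severity. It also makes a defined target time more useful, because the timing objective needs something to be measured against.

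Two further inferences are tempting and unsupported. One is that the repeated tests cannot fit into 40 min. The article gives no durations for imaging, sensory testing or questionnaires, so this would rest on assumed figures. The other is that the questionnaires serve no purpose after injection because they are not listed as outcomes. The secondary objective names questionnaires as a source of pain-mechanism indicators.

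**Conclusion.** The concern holds in a limited form. The endpoint definition and the visit schedule agree only at 60 min, and the visible text allows primary readings up to 40 min earlier (34 min for a post-walk score). The statement that 20 min secures the full effect is not supported by its own source figure. With ± read as an SD, about 10% to 16% of participants would have reached peak concentration by then, whichever of four plausible distribution shapes is used.

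The consequence for the SD, the effect estimate and the 17 mm responder split is a risk of distortion whose size the documents do not allow anyone to calculate. This is a point to clarify because it touches the quantities the study is meant to supply; it does not invalidate the design.

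**What to change.** Reconcile the Primary outcome measures and Experimental procedures sections as follows. No particular minute is proposed here; that choice is for the investigators.

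- Give the resting VAS and the walk-test VAS one nominal time after injection, a stated tolerance wide enough to hold both, and a fixed place in the test order, the same for every participant.
- Record clock time from injection for every post-injection measure, and report the share of primary readings inside the tolerance as a result under the outcome-timing objective.
- Withdraw the statement that 20 min secures the full effect, or support it with evidence that does so.
- If the full protocol already fixes the time and order, a sentence saying so is enough for the first item.

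The cost is a small amendment and a less flexible visit schedule. Recording clock times costs almost nothing. Because recruitment has begun, the report should also say which participants were assessed before the change.

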#### Secondary outcome measures

QST: the change scores of PPT, TSP and CPM from baseline to post intra-articular injection with bupivacaine or placebo.fMRI of the brain: the change in brain network activity from baseline to post intra-articular injection with bupivacaine or placebo.MOAKS^35^: the level of joint damage quantified by MOAKS and measured at baseline.Feasibility assessment: the number and percentage of eligible participants who are recruited and randomised to the study from the date of recruitment opening until the date of recruitment closing, as well as protocol completion rates and missing data rates.Feasibility assessment: evaluation of effective randomisation of participants to the study arms using a study-specific checklist and assessment of the randomisation protocol throughout the study.Feasibility assessment: a study-specific questionnaire will be administered to participants to assess the acceptability of the study at the end of the research visit.

### Data management and auditing

The collection, storage, processing and disclosure of personal information, data collection and management will comply with the requirements of the General Data Protection Regulation 2018. Handling of data will follow the policies and the procedures of the Sponsor (NUH NHS Trust) and the University of Nottingham. All personal data will be anonymised, and all further data analysis will be done without any reference to personal identifiable participant data.

The trial conduct will be monitored by the Sponsor (NUH NHS Trust).

### Statistical methods

Considering the feasibility nature of the study, no formal hypothesis tests will be performed to statistically compare the two study arms and descriptive statistics will be presented. Appropriate parametric or non-parametric statistics will be used according to the data characteristics.Summary statistics will be used to evaluate feasibility objectives such as the feasibility to recruit, timing measurements, to describe the sample and to inform the future main trial by providing power and sample size calculation. Participant acceptability feedback will be qualitatively synthesised using thematic analysis.Primary and secondary outcomes will be descriptively summarised by group as follows:Correlations between the change of pain score and QST measurements at baseline and after intra-articular injection with bupivacaine or placebo.Correlations between the change of pain score and brain network activity at baseline and after intra-articular injection with bupivacaine or placebo using predefined seeds in the pain processing regions.Correlations between the change of pain score and the level of joint damage quantified by MOAKS and measured at baseline.Estimates of between-group effect will be reported as estimates with 95% CIs without p values.In view of the exploratory nature of the study, missing data will not be imputed. The proportion of missing data for each outcome will be described.Differences in effects will be reported descriptively for primary and secondary outcomes between the following subgroups:Based on the stratification variable according to CAP-Knee Questionnaire scores with respect to whether pain is predominantly centrally or peripherally driven.The patients will be divided into responders and non-responders based on a cut-off value of ≥17 mm reduction in VAS post injection.^39^

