### Objectives

The primary objective of the UP-KNEE study is to evaluate the feasibility of a main definitive trial by:collecting data to inform sample size calculation;testing the recruitment process;Timing of the outcome measures;Testing the robustness of randomisation;Testing the integrity of the research protocol; andqualitative assessment of the acceptability of the methods of the feasibility study.The secondary objective of the study is to explore correlations of the analgesic response with indicators of central and peripheral pain mechanisms derived from MRI of the brain and knee, questionnaires and QST.

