### Hypothesis

For the future main trial, the hypothesis is that the analgesic response to a peripherally targeted intervention aiming to reduce knee pain will reveal two groups. The non-responders group will be patients with predominantly centrally driven pain characteristics, who will show less analgesic response to the peripherally targeted intervention while the responders group will be patients with predominantly peripheral pain who will show a greater analgesic response to the peripherally targeted intervention. Both groups will respond similarly to placebo. However, this feasibility study is not intended to test the hypothesis of the main trial.

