### Sample size

This is a feasibility study aiming to provide first proof of concept and descriptive statistics to power a future diagnostic trial. We aim to recruit 50 participants (25 to each group). This would be a large enough sample to assess the feasibility and inform a main trial based on statistical methodological papers providing recommendations about sample size requirements for feasibility and pilot studies.^17–19^

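### The listed correlations leave out questionnaires that the secondary objective names, and they use unadjusted within-arm VAS change with no stated contrast between the arms

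*Protocol article*

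**What the plan says.** The Objectives section of the protocol article gives the secondary objective in these words: "explore correlations of the analgesic response with indicators of central and peripheral pain mechanisms derived from MRI of the brain and knee, questionnaires and QST". The Psychometric questionnaires section lists ten instruments, among them painDETECT, the Pain Catastrophizing Scale and CAP-Knee.

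The Statistical methods section then lists three sets of correlations with the change of pain score, presented by group:

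- QST: "Correlations between the change of pain score and QST measurements at baseline and after intra-articular injection with bupivacaine or placebo"
- brain network activity, before and after injection, using predefined seeds
- joint damage on MOAKS at baseline

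The same section promises between-group estimates with 95% CIs and no p values. It also plans a descriptive comparison of effects between subgroups, one of them "Based on the stratification variable according to CAP-Knee Questionnaire scores with respect to whether pain is predominantly centrally or peripherally driven".

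The Hypothesis section expects patients with centrally driven pain to respond less to the peripheral intervention. It adds "Both groups will respond similarly to placebo", and then says that "this feasibility study is not intended to test the hypothesis of the main trial".

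**The concern.** There are two separate problems.

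**Coverage.** The objective names three sources of markers: MRI, questionnaires and QST. The list of correlations serves two of them. An analyst who follows the list would finish without relating painDETECT, catastrophising, depression, sleep, fatigue or anxiety scores to the pain response, although all are collected.

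**Interpretation.** Raw change is tied to baseline pain. A marker that tracks baseline pain will therefore correlate with change even if it has no bearing on how the drug works. A marker that tracks placebo response will do the same. Both effects are present in both arms, so only a comparison of the arms isolates the drug-related part. The section states no such comparison for the correlations. At stake is which markers go forward to the main trial: a correlation in the bupivacaine arm could be carried over as a sign of drug response when it is not one.

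**Working it through.** **The plan's own figure.** The Sample size section says "We aim to recruit 50 participants (25 to each group" and justifies this as "based on statistical methodological papers providing recommendations about sample size requirements for feasibility and pilot studies". No alpha, power, effect size or SD is given, so only 2 × 25 = 50 can be checked, and it agrees.

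**Coverage, side by side.**

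| Source named in the objective | Correlation listed | Other listed use |
|---|---|---|
| MRI of brain | yes | – |
| MRI of knee | yes (MOAKS) | – |
| QST | yes | – |
| Questionnaires: CAP-Knee | no | subgroup for differences in effects |
| Questionnaires: other nine | no | none |

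**Size of the baseline artefact.** The documents give none of these inputs. Assumptions: equal SDs before and after injection; pre-post VAS correlation ρ of 0.5 to 0.8 (both readings come from one visit, so the upper part of the range is plausible); marker-baseline correlation c of 0.3 to 0.5; and a marker related to change only through baseline pain.

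- corr(change, baseline) = −√((1 − ρ)/2)
- ρ = 0.5: −√0.25 = −0.50
- ρ = 0.8: −√0.10 = −0.32
- corr(marker, change) = c × corr(change, baseline)
- Smallest: 0.3 × 0.32 = 0.09 in size. Largest: 0.5 × 0.50 = 0.25 in size.

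**Simulation** (25 per arm, 4,000 replicates, pre-post correlation 0.5 to 0.7, correlations with VAS reduction):

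- *No drug moderation, marker tied to baseline only (c = 0.3 to 0.5).* The raw correlation is 0.11 to 0.25 in both arms. After baseline adjustment it is about 0.00.
- *Marker drives only the non-specific response.* The raw correlation is about 0.45 in both arms. After baseline adjustment it is still about 0.48, so adjustment alone does not remove placebo response.
- *In both situations above*, the mean difference between arms is about 0.
- *True drug moderation* (effect of 1 SD, falling by 0.4 SD per SD of marker; c = 0.3, pre-post correlation 0.7). The raw correlations are 0.12 on placebo and −0.37 on bupivacaine.

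One arm alone therefore cannot identify drug response, while the contrast between arms can.

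**Precision at 25 per arm** (Fisher z).

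- Within one arm, SE = 1/√22 = 0.21. For r = 0.3: atanh(0.3) ± 1.96 × 0.21 gives a 95% CI of −0.11 to 0.62.
- For the difference between arms, SE = √(2/22) = 0.30, and the half-width is 1.96 × 0.30 = 0.59 on the z scale.
- As a guide to what that means, a test of 0.5 against 0 would have about 45% power (56 per arm for 80%), and of 0.3 against 0 about 18% (167 per arm).

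These figures approximate the precision of an interaction slope. They do not give it exactly.

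**The case against.** The strongest reply is that the study should be held only to what it claims. The objective is to explore correlations, and correlations are planned. The effect-modification hypothesis belongs to the main trial and is expressly not tested here. Baseline adjustment and model form are commonly left to an analysis plan, which is not shown. Eight or more interaction estimates in 50 patients will be imprecise. Much of this stands, and it limits the point in four ways.

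- A reader might infer that the plan cannot separate drug response from placebo response or regression to the mean. The article does not support that. Taking the groups as treatment arms, both randomised arms are reported and can be compared. What is missing is a stated contrast.
- A reader might infer that questionnaires are ignored altogether. They are not: CAP-Knee strata get a descriptive comparison of treatment effects, which is already placebo-controlled.
- A reader might call the correlations with post-injection QST or brain measures an error. They are legitimate description and would mislead only if presented as prediction, which the article does not do.
- A reader might want to put a figure on the information lost by splitting CAP-Knee. No cut-point is stated, so none can be given.

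The reply does not reach the coverage gap. The article itself lists the correlations, and the list is narrower than its own objective. Nor does the lack of formal testing count against an interval estimate without a p value, which is the format the Statistical methods section already uses for between-group effects.

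**Conclusion.** The point holds in a limited form. The mismatch between the Objectives and Statistical methods sections is on the face of the article and needs no assumption: questionnaires are named as markers, none is in the correlation list, and nine of the ten have no listed analysis.

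The second part is a weakness of interpretation and not a fatal flaw. With raw change and no stated contrast, a single-arm correlation may contain an artefact of about 0.09 to 0.25 in size, under the assumed correlations given above. That is not negligible when an observed r of 0.3 in 25 patients has an interval of −0.11 to 0.62. The range is an illustration and not an estimate for this trial. The reading also takes the group summaries to be by treatment arm; if the arms were pooled, the placebo comparison would be lost and the concern would be stronger. In an exploratory feasibility study this is a worthwhile, low-cost improvement.

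**What to change.** In the Statistical methods section:

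1. Add the instruments from the Psychometric questionnaires section to the list of correlations, with CAP-Knee as a continuous score.
2. For each pre-injection marker, also report the arm-by-marker estimate from a model of post-injection VAS on baseline VAS, arm, marker and arm-by-marker. Give a 95% CI and no p value, and label it exploratory.
3. Keep the within-arm correlations and the CAP-Knee stratum comparison as description.
4. Label correlations with post-injection QST or brain measures as descriptive, not predictive.

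The cost is wording and a modest amount of analysis, since baseline VAS, arm and all markers are already to be collected. The downside is wide intervals: the SE is about 0.30 on the Fisher z scale for a between-arm difference in correlation. The report should say that a wide interval neither establishes nor rules out a marker.

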### Randomisation procedure and concealment of allocation

Eligible participants will be randomised in a 1:1 allocation ratio. An online computer service (SealedEnvelope.com) will be used for stratified randomisation to either intra-articular injection of bupivacaine or sodium chloride 0.9%. This facility generates codes that are concealed from the research team to either group. To mitigate against risk of allocation imbalance with respect to whether pain is predominantly centrally or peripherally driven, stratification will be based on the scores of the Central Aspects of Pain in the Knee (CAP-Knee) questionnaire, which will be sent to participants before the research visit. Participants will be randomised on a 1:1 allocation basis to either bupivacaine or placebo. To ensure blinding of the investigators to the participant’s group assignment, an authorised research nurse will prepare the allocated treatment. The randomisation schedule will be embedded by the research nurse in a secure password-protected folder to achieve allocation concealment.

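### No adjustment for baseline value or the CAP-Knee stratum is named for the between-group estimates; adjusting, and reporting the residual SD and baseline-to-post correlation, would give better precision and better planning figures at no cost

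*Protocol article*

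**What the plan says.** All references are to the protocol article.

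- **Outcomes.** Both primary outcomes are changes: "The change in pain score using a 100 mm VAS during the 6MWT from baseline to 1 hour after intra-articular injection with bupivacaine or placebo" and "The change in pain score using the VAS at rest from baseline to 1 hour after intra-articular injection with bupivacaine or placebo". Under Secondary outcome measures, PPT, TSP and CPM are also change scores.
- **Randomisation procedure and concealment of allocation.** Allocation is 1:1, and "stratification will be based on the scores of the Central Aspects of Pain in the Knee (CAP-Knee) questionnaire". The cut-off is not given.
- **Statistical methods.** Outcomes are summarised descriptively by group, with no hypothesis test. On the comparison of arms: "Estimates of between-group effect will be reported as estimates with 95% CIs without p values". On the choice of method: "Appropriate parametric or non-parametric statistics will be used according to the data characteristics". The stratum is given one role, as a subgroup: "Based on the stratification variable according to CAP-Knee Questionnaire scores with respect to whether pain is predominantly centrally or peripherally driven". Summary statistics are to supply the power and sample size calculation for the main trial.
- **Objectives.** Collecting data for that sample size calculation is the first item listed under the primary objective.

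The article does not call the estimates adjusted or unadjusted, and does not say which SD goes forward to the main trial.

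**The concern.** Outcomes defined as changes, descriptive summaries by group and no named covariate together suggest a difference in mean change with its interval, and the SD of change as the planning figure. That contrast makes no further use of two things the trial already has: each participant's baseline value and the stratum used in randomisation.

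Two things are at stake. The first is precision, with only 25 participants per arm. The second is the planning product itself. A main trial analysed with baseline as a covariate is sized on the residual SD of that model, and this cannot be worked out from the SD of change alone. If the SD of change is used in its place, the main trial will generally be larger than it needs to be.

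**Working it through.** **Inputs.** From the article: 25 per arm (Sample size), change outcomes, 95% intervals, and entry VAS of 30 to 80 mm (Eligibility criteria). The article gives no SD, correlation, effect size or power, so there is no power calculation to reproduce. Everything below on ρ, s, δ and the stratum effect is an assumption, shown over a range.

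**Baseline adjustment, equal SD s before and after, correlation ρ.**

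- Variance of change: 2s²(1−ρ)
- Residual variance with baseline as covariate: s²(1−ρ²)
- Ratio: (1−ρ²)/[2(1−ρ)] = (1+ρ)/2

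The table assumes s = 25 mm. Interval half-widths at 25 per arm are t × SD × √(2/25), with 48 df for change. The adjusted analysis uses 47 df and a factor √(1+1/46) for the covariate. Main-trial n per arm is 2(1.960+1.282)² × SD²/δ², rounded up, with δ = 10 mm, 90% power and two-sided 5%.

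| ρ | Variance ratio | SD ratio | SD change / residual (mm) | Half-width change / adjusted (mm) | n per arm change / adjusted |
|---|---|---|---|---|---|
| 0.4 | 0.70 | 0.84 | 27.4 / 22.9 | 15.6 / 13.2 | 158 / 111 |
| 0.5 | 0.75 | 0.87 | 25.0 / 21.7 | 14.2 / 12.5 | 132 / 99 |
| 0.7 | 0.85 | 0.92 | 19.4 / 17.9 | 11.0 / 10.3 | 79 / 67 |
| 0.9 | 0.95 | 0.97 | 11.2 / 10.9 | 6.4 / 6.3 | 27 / 25 |

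The variance ratio implies a main-trial n 30%, 25%, 15% and 5% smaller, and intervals 16%, 13%, 8% and 3% narrower. In the feasibility trial itself the gain is slightly less, because the covariate costs a degree of freedom.

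**Unequal SDs.** With b = baseline SD / post SD, the SD ratio is √[(1−ρ²)/(1+b²−2ρb)], and the slope of post on baseline is ρ/b. At b = 0.8 the ratio is 0.945 for ρ = 0.5, 0.990 for 0.7 and 1.000 for 0.8, where the slope is exactly 1. At b = 1.2 it is 0.778, 0.819 and 0.832. So the relevant condition is a slope different from 1, not a correlation below 1.

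**Chance imbalance.** The SE of the baseline difference is SD × √(2/25): 4.24 mm for an assumed SD of 15 mm and 5.66 mm for 20 mm. The probability of a difference above 5 mm in either direction is then 0.24 or 0.38. The change-score and adjusted estimates differ by (1 − slope) × imbalance. At ρ = 0.5 with equal SDs this is 0.5 × 5 = 2.5 mm.

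**CAP-Knee stratum.** This was simulated: 3,000 trials of 50, assumed strata of 34 and 16, arms balanced within stratum.

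- With no stratum effect, adding the stratum leaves the interval essentially unchanged (for example 0.495 s with or without it at ρ = 0.5).
- With an assumed stratum effect of 0.5 s on the post value, adding it to the baseline-adjusted model moves the mean half-width from 0.562 to 0.546 s at ρ = 0.3, 0.513 to 0.495 at 0.5, 0.431 to 0.409 at 0.7, and 0.283 to 0.248 at 0.9. These are reductions of about 3%, 4%, 5% and 12%.

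**The case against.** The strongest reply is that the article is silent rather than wrong. It names no estimator and leaves the method open. It condenses a fuller protocol, and covariates normally belong in an analysis plan, which is not shown. A change outcome is also fully compatible with adjustment: regressing change on arm and baseline gives the same arm estimate and residual SD as regressing the post value. This stands. A reader might infer that the plan has chosen an unadjusted analysis, and the text does not support that. What it supports is that the natural reading points to a change-score contrast and that nothing stated corrects this reading.

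A reader might also infer a biased or invalid result. That does not follow. Under randomisation the change-score contrast is unbiased, leaving out the stratum makes the interval conservative, no test is planned, and a larger planning SD oversizes the main trial rather than underpowering it. If the main trial were itself analysed on change scores, the SD of change would be the right input.

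The size of the gain is open too. Both measurements fall within one visit, so a high ρ cannot be excluded. The 30 to 80 mm entry window may compress the baseline spread and push the slope towards 1. CAP-Knee does have a place in the analysis, as a subgroup. The main-trial hypothesis expects central pain to lessen the response to bupivacaine but not to placebo, so its average effect across arms would be diluted.

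Finally, a report giving the SDs at baseline, post-injection and of change by arm would allow ρ, and hence the residual SD, to be worked out. The article does not commit to all three.

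**Conclusion.** The point holds as an improvement in precision and planning inputs, not as an error. If the section is followed on its natural reading, the between-arm estimates are valid but generally less precise than they could be, and the SD of change on its own is an incomplete planning figure. With equal SDs, adjusting for baseline narrows intervals by about 16% at ρ = 0.4, 8% at 0.7 and 3% at 0.9, and reduces the main-trial n by about 30%, 15% and 5%. These figures rest on assumed values of ρ and on equal SDs. The gain is zero where the slope of post on baseline is 1. The case for the stratum is weaker: little or nothing unless CAP-Knee predicts the outcome.

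**What to change.** For each primary VAS outcome, and for PPT, TSP and CPM, estimate the between-arm difference from a linear model of the post-injection value (or, equivalently, the change) on arm, baseline value and CAP-Knee stratum. Report it with a 95% CI and no p value, so the descriptive character is kept. Beside the raw means and SDs by arm, report the residual SD and the baseline-to-post correlation as planning figures for the main trial. If the analysis plan already specifies such a model, one sentence confirming it is enough.

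The cost is analysis wording and one model per outcome. No new data, visits or participants are needed, because the baseline values and CAP-Knee scores are already collected.
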